#### Blinding and Calibration of Reviewer

Two independent reviewers (an oral and maxillofacial surgeon) were assigned to evaluate and score each participant’s pretest and posttest sheets (Multimedia Appendix 1). Before data collection, the assessors underwent a calibration session to standardize the answer key for the multiple-choice questions (MCQs) and ensure consistent scoring. During the study, the assessors were blinded to the participants’ identities and allocation status, as they did not have access to names or group assignments. A final score for each participant was calculated.

Additionally, the reviewer will assess the participants’ training videos, focusing on training time completion, in-app lag or confusion, and skipped steps, to evaluate participants’ performance during training.

#### Informed Consent

Before participating in this study, the research assistant explained the trial flow and procedures for both the IR-based training and the conventional training. All participants will receive a brief introduction to the study and will have the opportunity to ask questions about the study procedures. After the participants provide their written informed consent (Multimedia Appendix 2), their basic health status will be recorded (Multimedia Appendix 3). Participants who are unable to give consent will be excluded from the study.

#### Inclusion Criteria

Participants will be enrolled from the Universitas Sumatera Utara, Hasanuddin University, and Padjajaran University. Eligible participants must be 20 years or older and be currently enrolled in their third year of dental school or have completed a minimum of seven semesters. They should have completed tutorials on both the open and closed methods of tooth extraction, possess knowledge of medical technology, and be capable of providing informed consent. Individuals who are unable to engage with virtual content for a minimum duration of 10 minutes while using an HMD will be excluded from participation.

#### Exclusion Criteria

Individuals who are unable to provide informed consent, possess health complications, display symptoms of cybersickness (eg, dizziness, disorientation, or vomiting) during training sessions, or are unable to complete the training session are excluded from participation. Additional exclusion criteria encompass a history of hallucinations, panic attacks, seizures, phobias (including claustrophobia and acrophobia), or active alcohol or substance abuse.

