### Trial Design and Study Population

#### Overview

This protocol is for a prospective multicenter randomized clinical trial, which began in March 2025 and is expected to end in November 2025. This protocol outlines our plan to assess the knowledge and skill enhancement of a pilot intervention across three centers: Hasanuddin University (Makassar, Indonesia), Padjajaran University (Bandung, Indonesia), and Universitas Sumatera Utara (Medan, Indonesia). A total of 90 dental students participated in the study (G*Power effect size 0.6, statistical power 85%). All participants enrolled in this study were randomly assigned to either an intervention group (n=15) or a control group (n=15) within each center. We used the block randomization method for the allocation of participants.

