**Enrollment**					
	Eligibility screen	t_–1_			
	Informed consent	t_–1_			
	Baseline assessment (MCQs^a^)	✓			
	Randomization	✓			

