#### Adverse Events

Participants who report feeling nauseated, dizzy, or disoriented, or having other health problems during a training session, will immediately be excluded from the activity. All such complaints will be recorded as cybersickness, and the occurrence of the condition will be noted for future evaluation.

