### Data Analysis Plan

The data were analyzed using SPSS v.22 (IBM Corp). Both descriptive statistics (frequency, percentage, mean, and SD) and inferential statistics (multivariate ANOVA) were used. A *P* value less than .05 was considered statistically significant.

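### Cybersickness and non-completion during training are written as exclusion criteria, so randomised students can be removed after allocation, mainly from the IR arm

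*Protocol article*

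**What the plan says.** Under Exclusion Criteria, students who "display symptoms of cybersickness (eg, dizziness, disorientation, or vomiting) during training sessions, or are unable to complete the training session are excluded from participation". The Adverse Events section repeats part of this: participants with nausea, dizziness, disorientation or other health problems "during a training session, will immediately be excluded from the activity". All such complaints are labelled cybersickness and noted for later evaluation.

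The Overview of the trial design says that everyone enrolled was "randomly assigned to either an intervention group (n=15) or a control group (n=15) within each center". Table 1 puts randomisation in the enrolment column and ticks both forms of training from the postrandomisation column onwards.

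The Intervention Group section describes 10 supervised minutes and then 40 further minutes in the HMD. The Control Group section describes a 10-minute lecture and 40 minutes on a phantom or mannequin, with no HMD.

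Both arms take an MCQ test, scored 0 to 100, before and after training. The Immersive Reality Neuroscience Questionnaire measures cybersickness among other things, and each of its parameters must reach a cutoff of 25.

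A separate criterion under Inclusion Criteria excludes anyone "unable to engage with virtual content for a minimum duration of 10 minutes while using an HMD". The article does not say when this is tested.

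**The concern.** An eligibility criterion should be decidable before allocation. These two are not: a student can meet them only by starting the allocated training. They are consequences of the intervention, yet they are written as reasons for not being in the trial.

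The two arms are also not equally exposed. Fifty minutes in an HMD can cause cybersickness; work on a mannequin does not involve the device. Non-completion and the other health problems named under Adverse Events can occur in either arm, so the exclusions fall mainly, but not only, on the IR arm.

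Two results are at stake. The first is the between-arm MCQ comparison, which would set IR students who tolerated and finished the session against a less selected control group. The second is the set of IR questionnaire scores. If the students with most symptoms leave before answering, the cutoff of 25 becomes easier to meet. For a pilot that says it explores feasibility, intolerance and non-completion are results in their own right.

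**Working it through.** **Timing and imbalance.** These follow from the text alone. Randomisation is at enrolment and training comes later, so an event during training is post-randomisation. HMD exposure is 10 + 40 = 50 minutes in the IR arm and none is described for control. The posttest follows training, and no section provides one for a student who has been excluded.

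**The plan's own figure.** The Overview states: "A total of 90 dental students participated in the study (G*Power effect size 0.6, statistical power 85"%. Three centres with 15 + 15 students give 45 per arm. The Data Analysis Plan sets a P "value less than .05 was considered statistically significant", without saying whether the test is one- or two-sided. Reading 0.6 as a standardised mean difference and using the noncentral t:

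- 85% power, two-sided: 51 per arm (102 in total)
- 85% power, one-sided: 41 per arm (82 in total)
- Power with 45 v 45: 80% two-sided, 88% one-sided

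So 90 is not reproduced from the stated inputs. That is a separate matter, but it sets the baseline here: the two-sided power before any exclusion is about 80%, not 85%.

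**Size of the possible bias.** The article gives neither the share of the IR arm that would be excluded nor how those students would have scored. Assumptions:

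- q, the share of the IR arm excluded, is 10%, 20% or 30%, with none excluded from control.
- ρ, the correlation between HMD tolerance and posttest score, is 0, 0.3 or 0.5.
- The least tolerant are excluded, the true effect is zero, and the comparison is an unadjusted posttest t test.

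Shift in the retained IR mean, in SD units = ρ × φ(z_q) / (1 − q), where φ is the standard normal density and z_q its q-quantile. The type I error is the rejection probability of the noncentral t with 45(1 − q) v 45 students and that shift.

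| q | φ(z_q)/(1 − q) | Shift, ρ = 0 / 0.3 / 0.5 | Two-sided type I error |
|---|---|---|---|
| 10% | 0.1755/0.9 = 0.195 | 0 / 0.058 / 0.097 | 5.0% / 5.8% / 7.3% |
| 20% | 0.2800/0.8 = 0.350 | 0 / 0.105 / 0.175 | 5.0% / 7.5% / 12.1% |
| 30% | 0.3477/0.7 = 0.497 | 0 / 0.149 / 0.248 | 5.0% / 9.7% / 18% |

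**Cross-check with a simpler model.** Shift = q × g, where g is the mean of retained students minus the mean of excluded students, in SD.

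- g = 0.5: for q = 10%, 20%, 30% the shift is 0.05, 0.10, 0.15 SD and the error 5.6%, 7.3%, 9.7%.
- g = 0: no bias.
- g = −0.5 (excluded students would have scored higher): the shift is the same size, against IR.

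**Power at 0.6 SD, two-sided.**

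- 45 v 45: 80%
- 40 v 45 (10% lost): 78%
- 36 v 45 (20% lost): 76%
- 31 v 45 (30% lost): 72%

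A 20% loss therefore costs about 4 to 5 percentage points (80.4% to 75.5%).

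**The case against.** The strongest objection is that the article never says these students are dropped from the analysis. Exclusion Criteria speaks of participation, and Adverse Events says they "will immediately be excluded from the activity", which may mean only the training session. Analysis sets are often left to an analysis plan, and none is shown. This stands in part: exclusion from the analysis is the natural consequence of an eligibility criterion, but it is not stated. It does not dispose of the point, because an analysis plan cannot recover a posttest that was never taken.

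A reader might infer that HMD intolerance is discovered only in students allocated to IR, because Table 1 lists no HMD trial. The article does not support that. The 10-minute criterion sits with eligibility, and Table 1 has an eligibility screen before randomisation whose content is not itemised. The timing is unstated, which calls for clarification. Even if tested beforehand, 10 minutes covers one fifth of a 50-minute session.

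A reader might also take bias in favour of IR as established. It is not. The outcome is an MCQ score, and nothing in the article links susceptibility to symptoms with that score. No bias and reversed bias are both possible. The type I error figures also ignore the pretest; a pre/post comparison would remove part of any selection that acts through baseline knowledge.

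Finally, this is a pilot with health, seizure and phobia exclusions already in place, so the number affected may be small. That bears on the size of the problem, not on whether the rule is sound.

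**Conclusion.** The point holds. The exclusion criteria contain two events that can occur only after randomisation. They fall mainly on the IR arm, and the text neither separates stopping training from leaving the trial nor provides a posttest for those affected. If the rule is followed as written, the between-arm MCQ comparison loses the protection of randomisation, and the IR cybersickness and usability scores come from a selected group.

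The size is unknown. Under the assumptions above it runs from no bias to 0.25 SD, with a type I error from 5% to 18%. The upper end needs 30% of the IR arm excluded and a correlation of 0.5. Bias towards IR is the more plausible direction, since students who tolerate or complete IR poorly are the ones removed, but that is a judgement. The loss of power is modest, and should not be read as a fall from the stated 85%.

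Correction is worthwhile whatever the true size, because under the current rule no data would be collected from which the bias could be checked.

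**What to change.** - Remove cybersickness during training and failure to complete the session from the exclusion criteria.
- Leave the rule for stopping a session unchanged, but state that stopping training is not leaving the trial.
- Give every randomised student the posttest and, where applicable, the questionnaires, and analyse all of them in the allocated arm.
- Report stopping and non-completion by arm as a feasibility and safety outcome. A completers-only analysis can be kept as a sensitivity analysis.
- State that the 10-minute HMD criterion is applied to all students at the eligibility screen, before randomisation.
- For the 60 students already enrolled, restore any who were excluded wherever a posttest exists or can still be taken. The third centre, not yet recruited when the article was written, can follow the revised wording in full.

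The cost is a change of protocol wording, a few extra posttests, and possibly a slightly smaller estimated IR effect. With all 45 v 45 analysed as randomised, this rule introduces no selection bias and two-sided power at 0.6 SD stays at about 80%.

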#### Intervention Group

Before the intervention, two oral and maxillofacial surgeons from each center will follow a comprehensive meeting held in Hasanuddin University, Makassar, to ensure consistent delivery of the interventions across centers and instructors. In addition, a facility assessment will be reported during the meeting to ensure that each center can deliver the intervention method using the same protocol.

Participants will be given a brief introduction and explanation of the study’s purpose. A research assistant will present the informed consent both in writing and verbally. This study has adopted standardized procedures for tooth extraction, using both open and closed methods.

The IR training session will be conducted in a standing position, where participants role-play as dentists. The training session will focus on open and closed dental extraction for the first molar tooth (tooth 46), supervised by two oral and maxillofacial surgeons in each center. For all training sessions, the first 10 minutes will be conducted under direct supervision. Participants will then continue their sessions for the last 40 minutes using in-app assistance (sound, highlighted areas, and arrows) without additional support for the remaining session.

The IR HMD wirelessly streams to an external device and will be used during the first session to monitor the participants’ training execution and provide guidance when necessary. Participants were required to complete a full round of training. This procedure included several steps: administering local anesthesia, making an incision and separating the tooth (in open method extraction mode), luxating and extracting the tooth, performing curettage, irrigating the wound, and suturing.

Following the completion of the procedure, participants are presented with the option to either restart the training sessions by selecting the reset button or terminate the session by choosing the exit button located in the menu area.

#### Control Group

Participants in the control group visited the Department of Oral and Maxillofacial Surgery at their origin center (Hasanuddin University, Padjajaran University, or Universitas Sumatera Utara) to receive a tutorial and hands-on laboratory instructions. Following a 10-minute lecture on the open and closed methods of dental extraction for the first molar tooth (tooth 46), participants will engage in hands-on training where they will extract artificial teeth from a phantom or mannequin, much like in the IR-based instructions. The hands-on training will have a duration of 40 minutes, starting from local anesthesia administration, gingival incision, tooth separation, tooth luxation, extraction, curettage, wound irrigation, and suturing. Tutorial and hands-on training will be guided by two oral and maxillofacial surgeons in each center. The trial flowchart is shown in Figure 1. To ensure a standardized methodology for conducting and reporting the trial, the SPIRIT (Standard Protocol Items for Intervention Trials) guidelines will be followed as shown in Table 1.

**Figure 1 figure1:**
[figure not shown]
Research flowchart. CVEQ: Clinical Virtual Evaluation Questionnaire; INRQ: Immersive Reality Neuroscience Questionnaire; IRTS: Immersive Reality Training System.

**Table 1 table1:** SPIRIT (Standard Protocol Items for Intervention Trials) participant timeline.

Timepoint		Enrollment (t_–1_ to t_0_)	t_0_	Postrandomization (t_1_; May 2025)	Closeout (t_x_; Nov 2025)
**Enrollment**					
	Eligibility screen	t_–1_			
	Informed consent	t_–1_			
	Baseline assessment (MCQs^a^)	✓			
	Randomization	✓			
**Intervention/comparator**					
	IRTS^b^ for tooth extraction		Tutorial of tooth extraction	✓	✓
	Hands-on training		Tutorial of tooth extraction	✓	✓
**Assessments**					
	MCQ questionnaires	✓			✓
	Knowledge improvement, posttest scores				✓
	Participants’ satisfaction with IRTS				✓

^a^MCQ: multiple-choice question.

^b^IRTS: Immersive Reality Training System.

#### Adverse Events

Participants who report feeling nauseated, dizzy, or disoriented, or having other health problems during a training session, will immediately be excluded from the activity. All such complaints will be recorded as cybersickness, and the occurrence of the condition will be noted for future evaluation.

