#### Participants’ Performance and Knowledge Improvement

To assess the practical skills and knowledge acquired, participants from both the intervention and control groups will be required to complete a pretest prior to the training and a posttest following the training session. The MCQs were administered in accordance with the reference textbook used by the Faculty of Dentistry, as outlined in the dentistry curriculum [46]. The scores ranged from 0 to 100, and the test scores of both groups were subsequently compared. The MCQs are centered on the procedural steps, instrumentation, and guiding principles pertinent to dental extraction. This examination is an established component of the curricula at Hasanuddin University, Padjajaran University, and Universitas Sumatera Utara, aimed at assessing students’ practical competencies and theoretical knowledge. Consequently, a comparative analysis test will be used to evaluate the scores obtained from the clinical skill training between these two groups.

Additionally, the performance of participants will be evaluated through recorded video training and will be assessed by an independent reviewer, focusing on training time completion, in-app lag or confusion, and skipped steps. The confidential paper-based data of participants will be securely stored in a locked storage unit at the study site, while electronic data will be maintained in a protected folder on a server at Hasanuddin University, Makassar, Indonesia.

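### The adverse-event rule records every health complaint in a training session as cybersickness, which can inflate that count and hides other adverse events

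*Protocol article*

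**What the plan says.** The Adverse Events section of the protocol article has two sentences. The first sets the trigger: "Participants who report feeling nauseated, dizzy, or disoriented, or having other health problems during a training session, will immediately be excluded from the activity". The second sets the recording rule: "All such complaints will be recorded as cybersickness, and the occurrence of the condition will be noted for future evaluation". The section gives no category for other events, no judgement of relation to the headset, and no restriction to one arm.

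The Exclusion Criteria use the term more narrowly. They name, as separate grounds, people who "possess health complications, display symptoms of cybersickness (eg, dizziness, disorientation, or vomiting) during training sessions".

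The article uses the term training session in two ways. The Intervention Group section uses it for IR training: "For all training sessions, the first 10 minutes will be conducted under direct supervision". The section on performance and knowledge improvement uses it for both arms: "participants from both the intervention and control groups will be required to complete a pretest prior to the training and a posttest following the training", with the word session completing that sentence. In the Control Group section, "participants will engage in hands-on training where they will extract artificial teeth from a phantom or mannequin"; no headset is described there.

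Cybersickness is also measured apart from the event record. Under Participants' Experience and Feedback, the Immersive Reality Neuroscience Questionnaire covers IR-induced symptoms in questions 16 to 20, and question 15 of the Clinical Virtual Evaluation Questionnaire covers side effects.

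**The concern.** The words all such in the recording rule reach back to everything in the trigger sentence, including "or having other health problems during a training session". Read plainly, a student who is injured during the session, or who has a headache from an unrelated cause, is entered as a case of cybersickness.

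Two things are at stake. The recorded count of cybersickness, the harm most specific to headset training, can be too high. And any other kind of adverse event disappears as a type. If only the label is kept, no later analysis can separate the events again.

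A third matter is open. If the rule covers both arms, a control student who feels faint while working on a mannequin is recorded as having cybersickness without headset exposure.

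**Working it through.** **No stated figure to reproduce.** The article gives no cybersickness rate, event count or safety sample size. The check is therefore a comparison of the text, followed by an illustration of size.

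**Step 1: scope of the term.**

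| Section | Covered by, or listed as an example of, cybersickness | Other health problems |
|---|---|---|
| Exclusion Criteria | Dizziness, disorientation, vomiting (as examples) | Listed separately, as health complications |
| Adverse Events | Nausea, dizziness, disorientation | Included in cybersickness |

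The two sections give one term two scopes. Their symptom lists also differ (vomiting in one, nausea in the other), although the list in the Exclusion Criteria is only by example.

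**Step 2: reach across arms.** The Adverse Events section refers to participants and to a training session, without naming an arm. Elsewhere the latter term is used for IR training and, once, for both arms. Both an IR-only reading and a both-arms reading are possible; neither is stated.

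**Step 3: weight of one event.** The Overview of Trial Design and Study Population gives 15 students per arm in each of three centers: 15 × 3 = 45 per arm. One miscoded IR student moves the recorded proportion by 1/45 = 2.2 percentage points.

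**Step 4: illustration with assumed rates.** Let c be the true cybersickness risk in the IR arm and b the risk of an unrelated complaint in either arm, independent of each other. Neither is in the documents. The ranges used are c = 5% to 20% and b = 0% to 10%.

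- Recorded IR risk = 1 − (1 − c)(1 − b)
- Recorded control risk, if the rule applies there = b
- Chance of at least one unrelated complaint in an arm of 45 = 1 − (1 − b)^45

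With c = 10%, the true expected number is 45 × 0.10 = 4.5 cases.

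| b (assumed) | Recorded IR risk | Recorded IR cases | Control cases, if covered | Chance of at least one per arm |
|---|---|---|---|---|
| 0% | 10.0% | 4.5 | 0 | 0% |
| 2% | 1 − 0.90 × 0.98 = 11.8% | 5.3 | 0.9 | 60% |
| 5% | 1 − 0.90 × 0.95 = 14.5% | 6.5 | 2.25 | 90% |
| 10% | 1 − 0.90 × 0.90 = 19.0% | 8.6 | 4.5 | 99% |

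For b from 2% to 10%, the falsely labelled share of IR cases, 1 − c divided by the recorded risk, runs from 1 − 0.20/0.216 = 7% (c = 20%, b = 2%) to 1 − 0.05/0.145 = 66% (c = 5%, b = 10%). The width of that range reflects the lack of any rate in the documents.

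**Step 5: the difference between arms.** If the rule covers both arms, with c = 10% and b = 5%, the recorded difference is 14.5% − 5.0% = 9.5 points, against a true 10 points. The distortion falls on the absolute count and on the loss of event types, and hardly on the contrast between arms.

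**The case against.** The strongest reply is that this is one loose sentence in a condensed article and that little depends on it. Several parts of that reply stand.

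- **A reader might infer that the rule makes the safety result wrong.** The documents do not support that. They define no adverse-event endpoint and no between-arm safety comparison, and occurrences are only to be noted for future evaluation. The questionnaires measure symptoms separately. The article does not say whether students who stop early still complete them, so how far they would back up the event record for those students is unclear.
- **A reader might infer that miscoding feeds the judgement that the system is suitable.** It does not. The cutoff of 25 is applied to questionnaire parameters, and nothing in the article routes event records into it.
- **A reader might infer that control complaints will certainly be miscoded.** That is one of two readings. The Control Group section speaks of a tutorial and hands-on training, and an IR-only reading is natural for a rule about cybersickness.
- **A reader might infer that the control arm is lost as a reference for background symptoms.** On the both-arms reading it is not: allocation is known, and Step 5 shows that the difference is nearly preserved. On the IR-only reading, control events are not miscoded. The two complaints cannot both be made.
- **The assumed rates have no anchor.** Students are screened for health problems and training lasts about 50 minutes (10 + 40), so unrelated complaints may be rare. At b = 0 there is no error.

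What the reply does not remove is the rule itself. Details of an event form may well sit in a fuller protocol, but this article does more than leave them out: it assigns every complaint to one named condition, and it conflicts with its own Exclusion Criteria.

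**Conclusion.** The point holds in a limited form. As written, the rule places open-ended health problems under cybersickness, contrary to the separation in the Exclusion Criteria. It can therefore inflate the recorded cybersickness count, by 2.2 percentage points of the IR arm for each miscoded student, and it hides any other type of adverse event. Whether it also labels control complaints as cybersickness is an ambiguity that the authors need to settle.

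The inconsistency and the loss of event types follow from the text alone. The 2.2 points rest on the planned 45 IR students. The expected counts in the illustration rest on assumed rates and show only what the rule could do. The conclusion does not extend to the questionnaire cutoff or to a comparison of harms between arms.

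**What to change.** Change the recording only; how students with complaints are managed is outside this point.

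1. Log each complaint by its actual symptom, its onset and the student's arm.
2. Reserve the term cybersickness for a predefined list of symptoms arising in headset users, and record other health problems under their own category.
3. State whether the rule applies to both arms.
4. Reconcile the wording and symptom lists of the Adverse Events section and the Exclusion Criteria.

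The cost is a small change to the event form and one extra table. The Results section says that 60 students from two centers had been enrolled and that recruitment at the third was still to come, so the new form could be used there from the start. Events at the first two centers can be recoded if the original complaints were kept. If they were not, the report should say that the count from those centers covers any health complaint.
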